#### Intervention programme

The menstrual pain management intervention programme consisted of twelve sessions:

• Session 1: Psycho-education

• Session 2 – 4: Deep breathing, progressive muscular relaxation and guided visualisation

• Session 5: Taking exercise

• Session 6: Distraction techniques

• Session 7 – 9: How your thoughts make you feel, challenging negative thoughts and using positive coping strategies

• Session 10: Problem solving

• Session 11: Medication

• Session 12: Planning for the future

Each weekly session was conducted with a group of 5–7 young women and lasted approximately 45 minutes. The session structure consisted of a recap of the previous session and feedback on how participants used the new technique, general information, topic related examples, group exercises and discussion, homework exercises and a session summary sheet. At the end of each session, participants interacted during a snack break which fostered a sense of group cohesion.

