The three primary outcome measures were administered at T1: baseline (pre-intervention), T4: 12 weeks from baseline (post-intervention) and T5: 3 months follow-up. Post intervention measures were administered by another researcher, independent of the research team, to minimise social desirability bias. The Pain Coping Scenarios Questionnaire and the Pain Knowledge Questionnaire were administered at two additional time points - T2: 5 weeks from baseline and T3: 10 weeks from baseline. These additional time point measures facilitated process evaluation to determine which elements of the intervention programme were most effective for this population.

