#### Quantitative analysis

Multivariate analysis of variance (MANOVA) will be used to examine differences in the primary and secondary outcome measures between the intervention and matched control groups. Within-groups differences will be measured at each time-point, including baseline. Baseline scores will be included as a covariate to allow for regression to the mean and a multiple regression model will be used. A step-wise method of regression analysis will be conducted with predictors entered using the backward method. This method will be used for exploratory model building and will be cross-validated by then randomly splitting the data. The dependent variables of interest will be strategies used to cope with pain and pain knowledge. The reliability of the Pain Coping Strategies Questionnaire and the Pain Coping Scenarios Questionnaire will be assessed by Cronbach’s alpha and validity will be assessed by correlating the measures against one other. Predictors will include the demographic characteristics of age and degree of intellectual disability as well as time since onset of menstruation; frequency and duration of menstruation; number and frequency of menstrual symptoms experienced and history, treatment and use of medication to manage gynaecological problems and other medical conditions.

Process evaluation will be conducted to assess change over time for the primary outcome measures. This will be done by looking at within groups differences at each of the assessment time points. To assist with process evaluation, sessions 2 – 5 focused on behavioural coping strategies and sessions 7 – 10 were dedicated to cognitive coping strategies.

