## Discussion

In this study, we evaluated the impact on pain coping and pain management knowledge, of a menstrual pain management programme for young women with intellectual disabilities. We expected participants in the intervention group to report the use of a greater number of coping strategies and have greater knowledge of pain management strategies at both T4 and T5, compared to control group participants.

The content of the menstrual pain management programme was adapted from the theory-based cognitive behavioural therapy programme “Feeling Better – A manual for carers working with people who have intellectual disabilities and chronic pain” [20]. The programme that was developed reflected the input from the parents/guardians of research participants, on both content and delivery methods. The PRP qualitative component ensured that the theory-based programme was specifically tailored to meet the needs of this population. As stakeholders, parents/guardians have insights into the training needs of their daughters and the possible challenges in delivering such a programme. Caregivers control access to medical/health services [3,38], so it is very important that they are involved with health interventions for those who are in their care.

A significant advantage to this study was the inclusion of process evaluation to determine which elements of a cognitive behavioural therapy programme work best for individuals with intellectual disabilities. Hunter [39] identified the need for clarification on effective components of CBT approaches for pre-menstrual symptoms and this is particularly relevant for this population. Moderator analyses of the outcome of the intervention will enable a better understanding of who this type of training is most effective with and under what conditions. Such information will enable us to optimize treatment for each individual into the future. For this reason, a number of variables which are assumed to be related to pain coping were measured in this study.

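### The quantitative process evaluation judges programme elements by within-group change under a single session order, so it can show when scores changed but not which element changed them

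*Protocol article*

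**What the plan says.** In the Protocol article, Quantitative analysis states that the process evaluation assesses change over time in the primary outcome measures, and gives the method: "This will be done by looking at within groups differences at each of the assessment time points". To help with this, it adds that "sessions 2 – 5 focused on behavioural coping strategies and sessions 7 – 10 were dedicated to cognitive coping strategies".

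The purpose is given under Primary outcome measures, where the T2 (5 weeks) and T3 (10 weeks) assessments are introduced: "These additional time point measures facilitated process evaluation to determine which elements of the intervention programme were most effective for this population". The Discussion repeats the claim: "A significant advantage to this study was the inclusion of process evaluation to determine which elements of a cognitive behavioural therapy programme work best".

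Intervention programme lists twelve weekly sessions in one sequence, with psycho-education as session 1 and, between the two blocks, "Session 6: Distraction techniques". No reordered version is described for any of the three intervention groups.

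Table 1 shows Pain Coping Scenarios and Pain Knowledge at T1 to T5, but Pain Coping Strategies only at T1, T4 and T5. Primary outcome measures also states: "Post intervention measures were administered by another researcher, independent of the research team, to minimise social desirability bias".

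**The concern.** A statement about which element works best compares components. The planned evidence is change within a group across intervals that differ in content and also in calendar time, number of previous administrations of the same questionnaire, and amount of programme already received. Nothing in the stated method separates these. A rise from T1 to T2 could reflect the behavioural sessions, the introductory session, or being asked the same questions again. A rise from T2 to T3 could reflect the cognitive sessions, the distraction session, or delayed benefit from the earlier block.

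At stake is a claim that the article presents as a main strength and intends to use in shaping later programmes. The comparison of intervention with control on the main outcomes is not affected.

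**Working it through.** **1. Windows against content.** Assume weekly sessions starting just after baseline, T2 at 5 weeks, T3 at 10 weeks and T4 at 12 weeks. This alignment is inferred from the article's timings; the article does not state it.

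| Interval | Sessions | Stated behavioural block (2–5) | Stated cognitive block (7–10) | In neither block |
|---|---|---|---|---|
| T1–T2 | 1–5 | 2–5 | none | 1 (psycho-education) |
| T2–T3 | 6–10 | none | 7–10 | 6 (distraction) |
| T3–T4 | 11–12 | none | none | 11 and 12 |

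Each block falls in one interval only, and always the same one. Block and interval are therefore completely confounded, and each window also holds a session assigned to neither block.

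**2. Outcomes against time points.** The method is stated for the primary outcome measures, of which there are three. Two have T2 and T3 values. Pain Coping Strategies does not, so it cannot show change over T1–T2 or T2–T3.

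**3. Size of the problem.** The article gives no figure for the process evaluation, so there is none to reproduce. Its power statement (over 95% for d = .50 with N = 36) concerns a repeated measures F test and does not cover a component comparison.

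The following is an illustration. Inputs: n = 18 per arm (Research design) and two-sided α = 0.05 (Sample size and power calculation). Assumed: a true block effect of zero; drift δ per interval of 0.2, 0.3 or 0.5 SD; correlation ρ between successive scores of 0.3 to 0.7; equal variances; t tests on change.

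- SD of change = √(2(1 − ρ)), which is 1.183, 1.000 and 0.775 for ρ = 0.3, 0.5 and 0.7.
- Within one arm, the noncentrality is δ√18 / SD of change, on 17 df. For δ = 0.3 and ρ = 0.5 it is 0.3 × 4.243 / 1 = 1.27.

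| Drift (SD) | Chance of a significant within-group change, ρ = 0.5 | Range over ρ = 0.3–0.7 |
|---|---|---|
| 0 | 5% | 5% |
| 0.2 | 12.6% | 10–18% |
| 0.3 | 22.5% | 17–34% |
| 0.5 | 51.6% | 39–73% |

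**4. What a between-arm contrast does.** If drift is equal in both arms it cancels, and the rate stays at 5%. For a true 0.5 SD difference in change over one interval, the noncentrality is 0.5√(18/2) / SD of change, on 34 df: 1.27, 1.50 and 1.94 for ρ = 0.3, 0.5 and 0.7. Power is 23%, 31% and 47%. The contrast does nothing about order, because no group received the blocks in another sequence.

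**The case against.** The strongest reply is that this is a condensed article on an exploratory pilot, and that the process evaluation does not rest on these numbers alone. Focus groups with participants, parents and staff address the same question about elements. That stands, and the criticism is confined to the quantitative strand.

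The outcomes also have some specificity. Scenarios responses are coded behavioural or cognitive, Knowledge items follow the programme's domains, and a Knowledge answer is credited only if the participant's example supports it. This limits gains from mere familiarity and offers a way to a better analysis, but the stated method makes no use of it in linking change to a block.

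The text under Primary outcome measures openly says that only Scenarios and Knowledge were taken at T2 and T3. The fault over Pain Coping Strategies is therefore one of wording in the analysis section, not concealment.

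Three stronger readings are tempting but unsupported:

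- A reader might infer that the control arm is ignored. The article does not say so. Within-group differences may include the controls' own change, Table 1 does not restrict T2 and T3 to one arm, and a between-group MANOVA is planned for the outcomes in general. What can be said is that no between-arm contrast is named for the process evaluation.
- A reader might infer that the change of assessor spoils the block comparison. It is placed at post-intervention, so it bears on contrasts involving T4 and possibly T5, not on T1–T2 or T2–T3. It is also a stated safeguard against bias.
- A reader might expect a ceiling on the seven-item Knowledge score, or an advantage for the block taught first. No baseline scores are given, so both are conjecture.

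**Conclusion.** The point holds for the quantitative strand. Within-group change under one fixed order cannot identify the more effective element, and for one of the three primary measures the interim evaluation cannot be done. The confounding follows from the design and needs no assumption beyond sessions running to the stated timetable. Its numerical size does rest on assumptions: with drift of 0.2 to 0.5 SD and correlations of 0.3 to 0.7, the chance of crediting an inert block rises from 5% to somewhere between 10% and 73%.

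This should be corrected before the process results are reported. It leaves the main between-group comparison untouched and does not discredit the focus groups.

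**What to change.** - For Pain Coping Scenarios and Pain Knowledge, replace the within-group comparisons with condition × interval contrasts of change over T1–T2 and T2–T3, provided T2 and T3 were collected in both arms. If they were not, say so and report the intervention arm descriptively.
- Analyse behavioural-coded and cognitive-coded Scenarios responses as separate outcomes. A pattern specific to a block would be a rise in its own code, relative to control, in its own interval.
- State that sessions 1 and 6 fall in the first and second windows and belong to neither block.
- State that Pain Coping Strategies cannot contribute to the interim evaluation.
- Interpret T3–T4 with caution because the assessor differs at post-intervention.
- Reword Primary outcome measures and the Discussion so that the quantitative conclusion is exploratory timing of change. Report the focus groups as a separate qualitative source on elements.

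The article says that pre- and post-intervention data collection is complete and analysis is in progress, so this changes analysis and wording only; the Scenarios coding is already part of the plan. The costs are a weaker claim about components and low power for each interval contrast (about 23–47% for 0.5 SD). Drift is removed only if it is similar in the two non-randomised arms, and the order confound remains whatever the analysis.

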On the Pain Coping Strategies Questionnaire, participants were asked to name all the different things they do to deal with their menstrual pain. Participant’s responses were coded as wellness-focused coping strategies or illness-focused coping strategies, based on the work of Jensen & Karoly [28]. Wellness-focused coping strategies included relaxation, exercise and distraction techniques. Illness-focused strategies included rest and use of medication. Coping strategies used were also coded as “behavioural” or “cognitive” in orientation, in line with the categorisation system used in the *Feeling Better* programme. The effectiveness of pain coping strategies was also assessed by asking participants to rate how well each of the strategies worked using three response options: “works very well”, “works sometimes”, “doesn’t work at all”. The Pain Coping Scenarios Questionnaire asked participants how they would cope with pain in four hypothetical situations i.e. during the night, at school/at their day programme, at home and during a social activity. This determined if participants could generalise techniques learnt during the intervention programme to situations in which they may experience menstrual pain. Again, coping strategies were coded as wellness-focused or illness-focused and as behavioural or cognitive in orientation. The Pain Knowledge Questionnaire [27] assessed knowledge of pain coping strategies using a seven item multiple choice questionnaire. Response options were “yes”, “no” and “don’t know”. The items on the scale reflect the core domains of the intervention e.g. relaxation, exercise, distraction, challenging negative thoughts. A clarifying question was asked following each correct answer (“Can you give me an example?”) to confirm that the participant had some knowledge related to their answer. If the participant answered the question correctly but the supplementary information provided demonstrated inaccuracies in knowledge, the response was not credited as correct.

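### The quantitative process evaluation is meant to show which programme elements work, but change by visit can at best compare blocks of sessions

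*Protocol article*

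**What the plan says.** The protocol article, under Primary outcome measures, states that the Pain Coping Scenarios and Pain Knowledge questionnaires "were administered at two additional time points - T2: 5 weeks from baseline and T3: 10 weeks from baseline", and gives the purpose: "These additional time point measures facilitated process evaluation to determine which elements of the intervention programme were most effective for this population". The Discussion presents this as a notable strength of the study.

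Under Quantitative analysis, the process evaluation is defined as change over time in the primary outcome measures, and the method follows: "This will be done by looking at within groups differences at each of the assessment time points". The same paragraph groups sessions 2-5 as behavioural and sessions 7-10 as cognitive.

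Two finer sources of data are described under Primary outcome measures. For the Pain Coping Strategies Questionnaire: "The effectiveness of pain coping strategies was also assessed by asking participants to rate how well each of the strategies worked". For the seven-item Pain Knowledge Questionnaire: "The items on the scale reflect the core domains of the intervention". Scenario answers are also coded as behavioural or cognitive. The Quantitative analysis section states no analysis by item, domain or strategy. The study aims and the Qualitative analysis section add focus groups, analysed thematically, which also address which elements helped.

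**The concern.** A stated aim about elements is paired with a stated method that works on whole intervals between visits. A rise in score between baseline and week 5 belongs to everything taught by then. It could be reported as showing that relaxation and exercise work, although one technique, or the opening education session, may account for all of it. The same rise could also come from practice with the questionnaire or the passage of time, since the contrast is within group.

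What is at stake is a secondary conclusion, not the primary comparison. It still matters: the Discussion relates this evaluation to a need to know which components of CBT are effective, and the Conclusion foresees use of the programme in school health education.

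**Working it through.** No power, sample-size or alpha figure bears on this point, so there is none to reproduce. The check places the sessions in the visit intervals.

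**Inputs**
- Sessions (Intervention programme): "The menstrual pain management intervention programme consisted of twelve sessions", held weekly. Session 1 is psycho-education; sessions 2-4 are "Deep breathing, progressive muscular relaxation and guided visualisation"; 5 exercise; 6 distraction; 7-9 thoughts and positive coping; 10 problem solving; 11 medication; 12 planning.
- Visits (Primary outcome measures): T1 baseline, T2 week 5, T3 week 10, then "T4: 12 weeks from baseline (post-intervention) and T5: 3 months follow-up".
- Measures by visit (Table 1): Coping Scenarios and Pain Knowledge at T1-T5; Coping Strategies at T1, T4 and T5 only.

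**Step 1: number of contrasts.** Four visits from T1 to T4 give 4 - 1 = 3 successive in-treatment contrasts for 12 sessions. T4-T5 lies after treatment. For Coping Strategies the only in-treatment contrast is T1-T4, which covers the whole programme.

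**Step 2: what each contrast contains.** The article does not say how session days line up with assessment days, so this is an assumption, shown over its plausible range.

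| Alignment | T1-T2 | T2-T3 | T3-T4 |
|---|---|---|---|
| A: session k in week k, visit after that week's session | 1-5 | 6-10 | 11-12 |
| B: session 1 in week 0, visit after that week's session | 1-6 | 7-11 | 12 |
| C: session k in week k, visit before that week's session | 1-4 | 5-9 | 10-12 |

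**Step 3: what can be told apart.**
- The three relaxation techniques (sessions 2-4) share one interval under A, B and C.
- Exercise joins them under A and B. Under C it falls in with distraction and the sessions on thoughts.
- The sessions on thoughts (7-9) share one interval under A, B and C. Problem solving joins them under A and B.
- The only session ever alone in an interval is session 12 (under B), which is planning and not a coping technique.

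**Step 4: how clean the blocks are.** Session 1 falls with the behavioural sessions under every alignment. Session 6 belongs to neither stated block, yet it falls with the cognitive sessions under A and C and with the behavioural sessions under B.

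**Step 5: confounding.** Every group meets the behavioural block first and the cognitive block second. A within-group difference between intervals therefore mixes content with elapsed time, repeat testing and carry-over from earlier sessions. The process-evaluation text states no contrast with controls.

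**Step 6: what the finer data can show.** Pain Knowledge items are available at five visits, but relaxation appears as a single domain among the examples given, so on those examples they do not separate breathing, muscle relaxation and visualisation. They measure learning. The effectiveness ratings exist only for strategies a woman names, at T1, T4 and T5, and measure perceived usefulness. With n = 18 per arm, one woman is 1/18 = 5.6 percentage points.

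**The case against.** The strongest reply is that the article never promises to separate one relaxation technique from another. The contrast it sets up is behavioural versus cognitive: the fourth study objective asks about it, strategies are coded that way, the sessions are grouped that way expressly for the process evaluation, and T2 and T3 fall near the ends of those groups. Read so, the schedule fits the question in part. This stands, and it is why the fix keeps the block comparison. It does not remove the impurity of the blocks, the fixed order or the absence of a stated control comparison. Nor does it fit the wider wording about elements.

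A reader might infer that the ratings and domain items are left unused. The document does not support that. Both belong to primary questionnaires whose change over time is to be assessed, nothing limits the analysis to total scores, and a condensed article may leave item-level detail to a fuller plan. All that can be said is that no such analysis is stated.

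It is also fair to say that focus groups take up the question of elements, as suits a mixed-methods study. They do not supply what the quantitative text claims for the T2 and T3 measures.

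**Conclusion.** The concern holds at the level of blocks. Followed as written, the quantitative process evaluation yields at most three in-treatment contrasts for twelve sessions, in a fixed order and within groups. It cannot support a conclusion about a single technique, and supports one about behavioural versus cognitive content only with caution. The exact make-up of each interval rests on the assumed alignment and shifts by one session. The count of three, and the inability to separate the relaxation techniques, do not change with it.

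Two stronger readings should be avoided. One is that the trial can say nothing about elements: coded answers, knowledge items, ratings and focus groups all bear on them. The other is that tabulating these data would isolate each technique's effect, which Step 6 rules out. For a pilot and exploratory trial this is a worthwhile, inexpensive improvement and not a fault in the main comparison.

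**What to change.** 1. State that score changes involving T2 and T3 will be interpreted only as behavioural versus cognitive blocks. Name the sessions in each interval as actually delivered, including where sessions 1 and 6 fell.
2. Set each of these changes beside the change in the control group over the same visits, where controls were assessed. Table 1 does not give the schedule by arm, so say which visits controls attended.
3. Add descriptive tables by arm: Pain Knowledge change by domain item and counts of behavioural- and cognitive-coded scenario answers at T1-T5; and, at T1, T4 and T5, the number of women naming each taught strategy and the number of those giving it the top effectiveness rating.
4. State that these tables show learning, uptake and perceived usefulness, not the separate effect of each technique, and read them alongside the focus-group themes.

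The cost is small. The article reports that pre- and post-intervention data collection is complete and analysis is in progress, so this is tabulation of data already collected plus a change of wording. The downside is small counts, so the added results are descriptive only and should carry no significance tests.
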